## Abstract

**Background:**

Loneliness is a widespread global issue among older adults that negatively impacts physical and mental health, cognitive functioning, quality of life, and longevity, while also burdening society with healthcare costs. Resulting from factors at individual, interpersonal, and community levels. Multi-level interventions targeting these levels show promise in addressing this complex issue.

**Objective:**

This trial aims to develop, implement, and evaluate a multi-level intervention comprising individual-, interpersonal-, and community-level components to reduce loneliness and enhance well-being among older adults in Hong Kong.

**Methods:**

This pragmatic, assessor-blinded, 4-arm cluster randomized controlled trial will evaluate a multi-level intervention among 1,344 community-dwelling lonely older adults living in poverty. Participants will be randomized equally to one of the four 6-month intervention groups delivered by trained volunteers: individual-level only, individual- + interpersonal-level, and individual- + interpersonal- + community-level interventions against an education-only control group. Data will be collected at six time points: baseline; 2, 4, and 6 months post baseline; and 12 and 24 months after intervention completion. Primary outcome is assessed by the Revised UCLA Loneliness Scale. Secondary outcomes include De Jong Gierveld Loneliness Scale, symptoms of anxiety and depression, perceived stress, life satisfaction, psychological well-being and sleep quality. Potential mediators will be assessed by mindfulness, self-compassion, emotion regulation, perceived social support, social network characteristics, and neighbourhood collective efficacy and identification. Analyses will follow the intention-to-treat principle, employing linear mixed-effects models, regression, mediation, and cost-effectiveness. Qualitative data collected via focus group discussions will be analysed thematically to gain deeper insight into participants’ experiences and perceptions of the different interventions.

**Results:**

This study will last for 4 years, starting from June 2025 to May 2029. Recruitment and enrolment will begin in March 2026. Data collection will commence in April 2026, followed by the start of intervention delivery.

**Conclusion:**

To our knowledge, this is the first study globally to implement a multi-level intervention targeting older adults experiencing loneliness and poverty. If proven effective, the multi-level intervention will establish a foundation for community-wide implementation, providing a timely, affordable, and scalable approach that leverages community social capital.

**Clinical trial registration:**

ClinicalTrials.gov, identifier NCT07123064.

## Introduction

Loneliness, defined as the subjective perception of a gap between desired and actual social connections (1), has emerged as a critical public health challenge (2). In Hong Kong, approximately 46% of older adults report experiencing loneliness (3), a prevalence shaped by age-related health decline, reduced mobility, and economic vulnerabilities (4, 5). Loneliness is associated with adverse physical and mental health outcomes and increased healthcare utilization, underscoring its importance as both social and health concern (6–12).

This issue is intensified among older adults living in poverty. Nearly 45% of Hong Kong’s aging population lives in poverty, largely due to demographic changes and inadequate retirement protections (13). Economic vulnerability not only threatens older adults’ financial security but also heightens their risk of loneliness by limiting access to social participation and community resources (3). Although loneliness affects individual across all socioeconomic backgrounds, interventions that specifically target economically disadvantaged older adults are essential for addressing health inequalities and addressing the compounded social and health challenges they face (14, 15). Therefore, it is imperative to develop effective and scalable interventions for this population.

Despite numerous efforts to mitigate loneliness among older adults, the most effective intervention remains undetermined (16–19). Loneliness arises from a complex interplay of factors spanning from individual, interpersonal, and community factors (20, 21). Increasingly, systematic reviews and meta-analyses suggest that interventions addressing multiple levels simultaneously may be more effective than single-level approaches, as they leverage on reinforcing mechanisms across social contexts (17–19, 22, 23). However, multi-level interventions are often complex, resource-intensive, and robust trials evaluating their incremental benefits and cost-effectiveness remain scarce. To our knowledge, no randomized trial has systematically integrated the individual-, interpersonal-, and community-level components to address loneliness among older adults.

Against this backdrop, the present study aims to address this gap by evaluating the incremental benefits of a multi-level interventions. Specifically, we examine whether augmenting an individual-level intervention with interpersonal and community components leads to greater and more sustained reduction in loneliness.

At the individual level, psychological interventions have shown promising results in reducing loneliness (24, 25). Mindfulness-based approaches foster present-moment awareness and emotional regulation (26, 27), while behavioral activation promotes engagement in meaningful and rewarding activities; both have shown effectiveness in alleviating loneliness (25, 28). In Hong Kong, these approaches were successfully adapted for telephone delivery by trained volunteers during the COVID-19 pandemic (29, 30, 96), although their effectiveness beyond pandemic remains uncertain. Meta-analyses further indicate that interventions combining cognitive behavioral therapy (CBT) with strategies to enhance social connection are among the most promising strategies for reducing loneliness (17, 19). CBT enables older adults to modify maladaptive thoughts and behaviors related to themselves and social situations (31). Supporting this, an RCT demonstrated that an eight-week internet-based CBT (ICBT) intervention incorporating functional behavioral model, cognitive restructuring, behavioral activation to increase social participation, and psychoeducation effectively reduced loneliness in adults (32). Drawing on this evidence, we will enhance our individual-level intervention by integrating a cognitive component adapted from the ICBT developed by Käll et al. (32), with a locally validated mindfulness-based intervention (29, 30, 96), delivered by trained volunteers via the telephone, a modality selected for its accessibility, low cost, and feasibility among older adults facing mobility, digital, or socioeconomic barriers.

At the interpersonal level, interventions that strengthen social networks and enhance relationship quality play a central role in mitigating loneliness, particular among socially isolated individuals (33). These approaches focus on identifying meaningful social ties, rebuilding existing relationships, and fostering new connections through structured engagement (34, 35). Interventions like Groups 4 Health (G4H) (36) and Community Navigator (37), which emphasize social group belonging, have demonstrated efficacy in reducing loneliness among university students and adults with anxiety or depression. G4H was selected as the foundation for this level because it is explicitly designed to enhance social group identification and belonging—a key protective mechanism against loneliness. Importantly, G4H has also been adapted and piloted in older adults, yielding promising improvements in social cohesion, social group connections, depressive symptoms, and overall well-being (38). Although social isolation and loneliness are distinct constructs, social isolation remains a significant risk factor for loneliness. Accordingly, we will implement an interpersonal-level intervention, by adapting and modifying the Groups 4 Health (39) programme to the local context, delivered via telephone, and facilitated by trained volunteers.

At the community level, social infrastructure and neighbourhood cohesion play a central role in mitigating loneliness. Access to local social resources and supportive neighbourhood environments protects individuals at risk of loneliness (40, 41). Evidence suggests that interactions with neighbours may confer greater benefits for mental, cognitive, and physical health—lower mortality risk—than family engagement alone (23). In Hong Kong, neighbourhood collective efficacy has been identified as a protective factor that buffers the adverse effects of poverty on loneliness (3). Community-based, event-driven community interventions have also demonstrated effective in improving older adults’ mental well-being by strengthening neighbourhood connections and fostering social cohesive environment (42). Since its launch in 2003, the Neighbours Every Day (NED) programme in Australia has successfully promoted neighborly engagement through locally organized events, leading to sustained improvements in neighbourhood affinity, social cohesion, and reductions in loneliness (43). These benefits persisted for at least 6 months, with participants reporting stronger neighbourhood ties and larger social networks than non-participants (44, 45). Thus, our community-level intervention will implement in-person, community-led events modeled after the Neighbours Every Day programme.

Notably, there is a lack of longitudinal data on the sustained effects of loneliness interventions on health, cognition, and healthcare utilization (46). To address this gap, the present study will conduct follow-up assessments over 2 years to compare the effectiveness of the individual only, individual + interpersonal, and individual + interpersonal + community interventions against an education-only control group (Figure 1). In addition, we will examine the mechanisms through which these interventions exert their effects and assess their cost-effectiveness to inform resource allocation. This study will clarify not only the comparative effectiveness of each intervention level but also the underlying mechanisms and cost-effectiveness, providing essential evidence for the scalable implementation of community-based programmes.

**Figure 1 fig1:**
[figure not shown]
Illustration of multi-level interventions.

### Objectives

This primary objective of this study is to develop, implement, and evaluate a multi-level intervention comprising individual-, interpersonal-, and community-level components to reduce loneliness and enhance well-being among older adults in Hong Kong. The specific goals are to:

Evaluate the short-term effectiveness of the individual-level intervention, compared with an education-only control group in reducing loneliness.Assess the incremental benefit of adding an interpersonal-level intervention to the individual-level intervention in further reducing loneliness, compared with the individual-level intervention alone.Assess the incremental benefit of adding a community-level intervention to the combined individual- and interpersonal-level intervention in reducing loneliness.Examine potential mediators through which individual-, interpersonal-, and community-level interventions influence loneliness outcomes.Examine the long-term effects of the individual-level only, individual- + interpersonal-level; and individual- + interpersonal- + community-level interventions, compared with an education-only control group, on loneliness, physical and mental health, cognitive functioning, and healthcare utilization.Evaluate the cost-effectiveness of individual-level only, individual- + interpersonal-level; and individual- + interpersonal- + community-level interventions compared with education-only control group.

## Methods

### Study design

This study will employ a single-blinded, four-arm cluster randomized controlled trial to evaluate the effectiveness of reducing loneliness of an (i) individual-level only, (ii) individual- + interpersonal-level, (iii) individual- + interpersonal- + community-level interventions, compared to (iv) an education-only control group. This study will span across 4 years, commencing June 2025 to May 2029, to allow sufficient time for recruitment, intervention delivery, and both short- and long-term follow-up assessments. Figure 2 shows the CONSORT flow diagram. All study procedures will strictly adhere to the SPIRIT guidelines (Standard Protocol Items: Recommendations for Interventional Trials) as detailed in Table 1 (47).

**Figure 2 fig2:**
[figure not shown]
CONSORT flow diagram.

**Table 1 tab1:** Schedule of enrolment, interventions, and assessments for SPIRIT 2025.

	Study period						
	Enrolment		Post-randomization				Close-out
Timepoint	−*t*_1_	*t* _0_	*t* _1_	*t* _2_	*t* _3_	*t* _4_	*t* _5_
Enrolment							
Eligibility screen	×						
Informed consent	×						
Randomization		×					
Interventions							
First-arm (individual-level only)			×				
Second-arm (individual- + interpersonal-level)			×	×			
Third-arm (individual- + interpersonal- + community-level)			×	×	×		
Fourth-arm (education-only control group)			×	×	×		
Maintenance				×	×		
Assessments							
Primary outcomes							
Revised UCLA Loneliness Scale (59, 60)		×	×	×	×	×	×
Secondary outcomes							
De Jong Gierveld 6-item Loneliness Scale (61, 62)		×	×	×	×	×	×
Pittsburgh Sleep Quality Index (63, 64)		×	×	×	×	×	×
Satisfaction with Life Scale (65, 66)		×	×	×	×	×	×
Activities of daily living (73)		×				×	×
Instructional activities of daily living (74, 75)		×				×	×
Physical Symptoms Inventory (76, 77)		×	×	×	×	×	×
Charlson Comorbidity Index (78)		×				×	×
6-Minute Walking Test (79, 80)		×				×	×
Perceived Stress Scale (67, 68)		×	×	×	×	×	×
Hospital Anxiety and Depression Scale (69, 70)		×	×	×	×	×	×
Hong Kong Montreal Cognitive Assessment (71, 72)		×				×	×
Mediators							
Mindfulness Attention Awareness Scale (81)		×	×	×	×	×	×
Self-Compassion Scale-Short Form (82, 83)		×	×	×	×	×	×
Emotion Regulation Scale-Cognitive Reappraisal subscale (84, 85)		×	×	×	×	×	×
Multidimensional Scale of Perceived Social Support (86, 87)		×	×	×	×	×	×
Lubben Social Network Scale (88, 89)		×	×	×	×	×	×
Neighbourhood Collective Efficacy Scale (90, 91)		×	×	×	×	×	×
Cost-effectiveness							
Quality of Life Measures (92, 93)		×	×	×	×	×	×
Use of healthcare services		×	×	×	×	×	×
Demographics							
Age, gender, number of children, education level		×					
Marital status, living with family members		×				×	×
Economic activity status, house		×	×	×	×	×	×
Usage of senior citizen center or service		×	×	×	×	×	×
Usage of community/Home care services		×	×	×	×	×	×
Household income in the past month		×	×	×	×	×	×

### Public housing in Hong Kong

Public housing system in Hong Kong is a cornerstone of the city’s housing policy, managed by the Hong Kong Housing Authority and the Hong Kong Housing Society, and primarily serve low-income households. There are approximately 260 public housing estates across 18 districts, providing a suitable setting for identifying and recruiting economically disadvantaged older adults (48). Eligibility for public rental housing is determined by means testing and residency requirement.

### Sampling and two-stage cluster randomization

Our study will employ a cluster randomized controlled trial (cRCT) design, with public housing estates as the units of randomization. A cRCT was selected because the community-level intervention is delivered at the cluster-level and is likely to influence social interactions among residents within the same estate, making individual randomization impractical and increasing the risk of contamination. All individuals within each cluster will receive the same intervention, outcomes will be measured at the individual level, and analyses will account for clustering effects (49).

A two-stage cluster-random sampling approach will be used. In the first stage, 32 clusters will be randomly selected from the 260 public rental housing estates across Hong Kong and assigned to one of the four intervention arms by an independent researcher using 
*Random.org*
. The number of clusters may be adjusted if recruitment feasibility or cluster sizes vary. To minimize contamination, public rental housing estates assigned to different study arms will be geographically separated by at least 5 km, with a reasonable walking time of approximately 30 min or more. Figure 3 illustrates several estates located at least 5 km away from Oi Man estate, situated in the Kowloon City District. These estates include Tsz Hong Estate and Choi Wan II Estate in Wong Tai Sin District, as well as Wan Hon Estate in Kwun Tong District, with a walking time of at least 85 min. This spatial separation strategy is designed to reduce interaction between participants from different intervention arms, thereby maintaining the integrity of our intervention effects. In the second-stage, public rental housing units within each selected estate will be randomly sampled, and eligible residents will be invited to participate. This two-stage approach ensures an unbiased representation of older adults within each estates, while accounting for variation in cluster size.

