### Allocation concealment and blinding

Randomization will be conducted by an independent researcher, and allocation will remain concealed from other researchers and participants until assignment. Outcome assessors will be blinded to participants’ intervention allocation. Participants will be partially unblinded, as they are aware of the intervention they receive, but they will be blinded to study hypotheses. Interventionists will be unblinded due to the nature of the interventions. To further reduce contamination, participants will be asked not to discuss the intervention with residents from other estates during the study period.

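### The sampling section assigns estates to arms before residents are invited, Table 1 randomizes after consent, and under the first order nothing stated keeps the arm from those who recruit or are recruited

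*Protocol article*

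**What the plan says.** The design is a cluster trial "with public housing estates as the units of randomization". Under Sampling and two-stage cluster randomization, the first stage covers both selection and allocation: "32 clusters will be randomly selected from the 260 public rental housing estates across Hong Kong and assigned to one of the four intervention arms". The next stage reaches individuals: "In the second-stage, public rental housing units within each selected estate will be randomly sampled, and eligible residents will be invited to participate". The same section adds that "public rental housing estates assigned to different study arms will be geographically separated by at least 5 km" and that "The number of clusters may be adjusted if recruitment feasibility or cluster sizes vary".

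The section on concealment and blinding names who randomizes: "Randomization will be conducted by an independent researcher". On how long the arm stays hidden, it says that "allocation will remain concealed from other researchers and participants until assignment". Blinding applies to those who assess outcomes; participants know which intervention they receive, and interventionists are unblinded. The Measures section extends assessor blinding to all assessments, baseline (T0) included.

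Table 1 ("Schedule of enrolment, interventions, and assessments for SPIRIT 2025") marks eligibility screen and informed consent at −t1 and randomization at t0, the column that also holds the baseline measures.

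**The concern.** In a cluster trial, randomizing the clusters protects the comparison only if the people recruited within them are identified and consented without regard to the arm. If an estate's arm is settled and can be known before its residents are approached, two things can vary by arm: who is judged to meet the criteria, and who says yes.

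This setting is exposed to both. The criteria in the Participants section rest on self-reported material deprivation and a 3-item loneliness score, the latter close in content to the primary outcome. The arms ask very different things of a participant. A resident who would accept occasional messages may decline weekly calls or group events, and the reverse is possible too. At stake is the contrast in loneliness over time: the estimated effect could combine the effect of the intervention with a difference in who joined.

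**Working it through.** The point concerns sequence and has no figure of its own to reproduce, so the sections are set side by side.

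**1. There is only one randomization.** The estate is the unit, so the allocation step in the sampling section and the randomization row in Table 1 must be the same act. With 1,344 participants in 32 estates, 1,344 / 32 = 42 per estate on average, and 32 / 4 = 8 estates per arm if split equally. Knowing one estate's arm reveals the arm of all of its roughly 42 recruits.

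**2. The two orders.**
- Sampling section: select estates → assign arms → sample units → invite eligible residents.
- Table 1: screen and consent (−t1) → randomize (t0).

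These cannot both hold. Table 1 also leaves open whether T0 precedes randomization, because both sit in one column.

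**3. What the concealment sentence covers.** It ends at assignment. Under Table 1's order, that protects screening and consent. Under the sampling section's order, it is not stated to protect any step after stage one, and every contact with residents comes after stage one.

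**4. Who is stated to be unaware of the arm.** Outcome assessors, including the T0 interviewers. Nothing comparable is stated for those who screen, invite and consent, and the article does not say whether they are the same people as the interviewers.

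**5. How far the offers differ** (Table 2 and the Structure section, scheduled contact):
- Control: six monthly messages.
- First arm: 8 × 60 + 16 × 15 = 720 min (12 h), by telephone over 24 weeks.
- Second arm: 16 × 60 + 8 × 15 = 1,080 min (18 h), by telephone over 24 weeks.
- Third arm: 16 × 60 = 960 min by telephone over 16 weeks, then 4 × 120 = 480 min in person, 1,440 min (24 h) in all.

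**6. What the other safeguards reach.**
- Random sampling of units limits whom recruiters approach. It does not control who is judged eligible or who consents.
- Intention-to-treat analysis keeps participants in the arm in which they were recruited. It preserves a recruitment difference and does not remove it.
- The mixed model includes T0 and group-by-time terms, so a difference in baseline level need not bias the change contrasts. A difference in the course that recruits would have followed anyway could do so.

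**7. Size.** A simple form is: shift in arm mean = share recruited differently × their difference in trajectory. The document gives neither factor. It also gives no SD for the 0.087-unit target difference, so there is no stated benchmark in SD units. No number is offered.

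**The case against.** The strongest reply is that the protocol may already intend the safe order. Table 1 shows it. Promising to conceal allocation from participants until assignment makes little sense if assignment happens before anyone is a participant, so that sentence fits Table 1 better than the sampling section. Generating an allocation is also not the same as releasing it: the independent researcher could assign all 32 estates at the outset and tell nobody. Units are sampled at random, eligibility uses fixed cut-offs, and T0 interviewers are blinded. Finally, a journal article may leave recruiter blinding and the information sheet to the full protocol.

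Much of this stands. A reader might infer from the sampling section that recruitment takes place with the allocation known. The document does not support that: nowhere does it say that recruiters or residents know the arm. A reader might also be tempted to attach a size to the bias, but any such figure would rest on assumed inputs alone.

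The contradiction remains. The missing detail on recruiters would not be a point by itself. It becomes one because the article states an order under which that detail decides whether the comparison is protected, and elsewhere states the opposite order.

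**Conclusion.** The concern holds in conditional form. The sampling section and Table 1 give incompatible sequences, and the concealment sentence does not say which act it means by assignment. If the sampling section is followed as written, no stated safeguard keeps the estate's arm from those who screen, invite and consent, or from the residents. Eligibility judgements and consent could then differ by arm, in a way that the planned analysis would not be able to remove.

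The conclusion rests on two readings: that the stage-one assignment is the trial's only randomization, which the stated unit of randomization supports, and that the arm is not withheld after stage one, which the article neither states nor rules out. The direction and size of any bias cannot be derived from the document. It should be settled before enrolment, planned for March 2026, because differential recruitment cannot be undone afterwards.

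**What to change.** Make the sampling and concealment sections match Table 1.

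- Select the 32 estates first. The independent researcher already named may generate the allocation then, but withholds each estate's arm.
- In each estate, or batch of estates, complete unit sampling, screening, consent with one common information sheet, and T0. Only then release the arm. State that T0 precedes release, since Table 1 does not settle this.
- If estates are released in batches, keep estates less than 5 km apart in the same batch. Under the separation rule such estates must share an arm, so releasing one would reveal the other.
- Bring in any estate added under the clause on adjusting cluster numbers by the same procedure.
- If full completion before release is not feasible, state that those who screen and consent residents are unaware of the arm and that residents in all estates receive the same information before consent.

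The cost is a change of wording and a short wait in each batch between T0 and the start of the intervention, during which volunteers are matched to arms.

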### Sample size estimation

Based on a previous cluster randomized controlled trial designed to detect a difference between control and intervention groups for a continuous outcome (i.e., UCLA Loneliness Scale), an estimated variance was calculated at a two-tailed 5% level of significance, power of 95%, targeting a 0.087 unit difference on the UCLA Loneliness Scale while maintaining a relative precision of ±3.0% (49–52). Taking into account a 15% attrition rate across 24 months (53), unequal cluster sizes, intervention non-adherence, and potential ICC variability of *ρ* = 0.028, an effective sample size of 1,344 participants will be required, with 336 participants in each arm.

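### No balancing on estate characteristics is described for the 32 estates (about 8 per arm), and the 5 km separation rule restricts the assignment without balancing it

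*Protocol article*

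**What the plan says.** All of this is in the protocol article.

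- **Unit.** Sampling and two-stage cluster randomization sets the design up "with public housing estates as the units of randomization".
- **Selection and assignment.** The same section states that "32 clusters will be randomly selected from the 260 public rental housing estates across Hong Kong", and that these are "assigned to one of the four intervention arms by an independent researcher", with Random.org as the tool.
- **The one restriction.** It then requires that "public rental housing estates assigned to different study arms will be geographically separated by at least 5 km", for the stated purpose of limiting contamination. It does not say how this rule is combined with the random draw.
- **Number of estates.** "The number of clusters may be adjusted if recruitment feasibility or cluster sizes vary".
- **Equal arms.** The abstract says "Participants will be randomized equally to one of the four 6-month intervention groups", and Sample size estimation gives "an effective sample size of 1,344 participants will be required, with 336 participants in each arm".
- **Analysis.** Planned statistical analysis specifies a GLMM with a random intercept for cluster and fixed effects for time point (T0 to T5), group and their interaction, with GEE as a sensitivity analysis. It names no estate-level covariate. Covariate adjustment appears only as a capability of the software.

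No section mentions strata, matching, minimisation or a balance constraint on estate characteristics.

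**The concern.** Eight units per arm is few for chance alone to balance. The estates are drawn from about 260 across 18 districts, and the article itself expects cluster sizes to vary. It also argues, in the Introduction, that neighbourhood collective efficacy buffers the effect of poverty on loneliness, and it measures that trait as a mediator. So the plan treats neighbourhood-level features as relevant to the primary outcome, yet describes nothing that keeps them similar across arms.

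The 5 km rule adds to this. Two estates less than 5 km apart cannot be in different arms, so they must share an arm or one must be left out. Chains of close estates are tied together in the same way. Arms may then follow geography more closely than a free draw would allow, and any trait patterned by area would follow with them.

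At stake are the precision of the arm contrasts and how convincing they look. The specific goals include incremental comparisons between adjacent arms, so a visible difference in the type of estate between two active arms would invite doubt about the result.

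**Working it through.** **Inputs from the article.** 32 estates, four equal arms, 1,344 participants, 336 per arm, ICC 0.028, 15% attrition, two-sided 5% level, 95% power.

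**Structure.** 32/4 = 8 estates per arm; 1,344/32 = 42 participants per estate; 8 × 42 = 336. The plan's arm size fits 8 estates per arm, although the figure 8 is derived and not stated.

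**Imbalance on one estate trait, no balancing.** Take a trait scaled to SD 1 across estates, roughly normal and independent between estates (an assumption, as the article gives no estate data).

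- SD of the difference between two 8-estate means = √(1/8 + 1/8) = 0.5.
- One given pair: P(|difference| > t) = 2 × [1 − Φ(t/0.5)].
- Any of the six pairs: probability that the range of four independent means exceeds t, from 100,000 simulated allocations.

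| Gap | One given pair | At least one of six pairs |
|---|---|---|
| > 0.5 SD | 32% | 75% |
| > 0.75 SD | 13% | 44% |
| > 1 SD | 4.6% | 19% |

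The median largest pairwise gap is 0.70 SD. With three independent traits, a given pair shows at least one gap above 0.5 SD with probability 1 − (1 − 0.317)³ = 68%.

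These figures treat the 32 estates as freely assignable. If the 5 km rule ties estates together, fewer units are assigned independently, and imbalance on area-patterned traits would tend to be larger. The article gives no estate list, so this cannot be sized.

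**Scale on the outcome.** With ICC 0.028, the between-estate SD is √0.028 = 0.167 outcome SD. Chance estate differences then give a single-time-point arm contrast an SD of √(0.028 × 2/8) = 0.084 outcome SD. For comparison, the design effect is 1 + 41 × 0.028 = 2.148, so effective n per arm is 336/2.148 = 156.4. The difference detectable with 95% power is (1.960 + 1.645) × √(2/156.4) = 0.41 SD, or 0.42 SD after 15% attrition (35.7 per estate, design effect 1.972, effective n 144.9).

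**What balancing would achieve (simulation, ignoring the 5 km rule).**

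- *Stratifying on one trait.* The chance that some pair differs by more than 0.5 SD falls from 78% with no strata to 38% with two strata and 5% with four. The starting value is 78% and not 75% because the trait is scaled within the 32 drawn estates.
- *Drawing from the best-balanced 10% of allocations on three traits.* The chance of any gap above 1 SD, for any pair and any trait, falls from 51% to about 0%. Above 0.75 SD it falls from 86% to about 15%; above 0.5 SD only from 99% to 88%. Constrained allocation removes the large gaps but not all of the small ones.

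**The case against.** Four arguments count against the point.

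*The article is condensed, and a fuller protocol may name balancing factors.* True, and if it does, the point falls away. But the article describes the unit, tool, number and restriction in some detail, and the one restriction it gives is about contamination.

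*Simple cluster randomisation is valid.* This stands. A reader might infer that imbalance confounds the arm contrasts, but chance imbalance after a random draw is not systematic bias. The planned model also has T0 among the time points, a cluster intercept and group-by-time terms. An estate difference that is constant over time therefore largely cancels from the group-by-time contrast. What remains are traits that influence how loneliness changes.

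*The effect on the outcome is small.* Largely accepted. If a trait explained 25–50% of between-estate variance (an assumption), a 0.5 SD gap would shift the single-time-point outcome by 0.5 × 0.167 × √0.25 to 0.5 × 0.167 × √0.50, that is 0.04 to 0.06 outcome SD. That is well below the 0.41–0.42 SD detectable difference, and the stable part of it cancels.

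*Balancing on district may clash with the 5 km rule.* Also accepted. It limits how far geography can be balanced, and the fix has to respect that.

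A reader might also infer from the mention of Random.org that each estate is drawn independently and without restriction, so that unequal arms are likely. The document does not support this: it names a tool and not an algorithm, states equal arms, and imposes the separation rule. Nor can a gain in effective sample size be read off a reduced ICC, because that calculation belongs to a single-time-point comparison and not to the planned contrast with T0.

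**Conclusion.** The point holds as a cheap improvement, not as an error that invalidates the trial. The assignment as described has no balancing on estate characteristics, and its only restriction can align arm with geography. With 8 estates per arm, a gap above 0.5 SD on a given trait somewhere among the arms is likely (75%), while one above 1 SD is not (19%). The cost falls mainly on precision and credibility, through traits that affect change in loneliness.

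The conclusion rests on 8 estates per arm (derived, and open to change since the number of clusters may be adjusted), on roughly normal and independent estate traits, and on the absence of balancing factors in any fuller protocol.

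**What to change.** Before any assignment:

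1. Select and list all 32 estates, settling any change in their number at this stage.
2. Enumerate or sample the allocations that satisfy both the 5 km rule and 8 estates per arm.
3. Rank these on balance in estate size and share of residents aged 65 and over, adding broad region only as far as the 5 km rule allows. Have the independent researcher draw one at random from the best-balanced subset.
4. If too few allocations qualify for a meaningful random draw, revise the estate list before drawing.
5. Include the few balancing factors in the GLMM and the GEE together with their interactions with time. Main effects alone would barely alter the group-by-time contrast.
6. State the procedure, including how the separation rule is applied, in the protocol.

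The cost is a script before allocation, estate-level data on the chosen factors, and a few estate-level degrees of freedom out of 32 clusters, so the list of factors should stay short. Whether enough allocations satisfy both conditions cannot be judged from the article and has to be checked on the actual estate list. The allocation step is possible only before estates are assigned.
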